## Abstract

**Introduction:**

Over the past decades, interest in second breast-conserving therapy (BCT) has increased due to, among others, advances in radiotherapy techniques. Preoperative partial breast irradiation (PBI) is an experimental treatment for patients with low-risk primary breast cancer. This approach can downstage the tumour and may possibly reduce toxicity and improve cosmetic outcomes compared with postoperative radiotherapy. This study aims to evaluate the feasibility of single-dose preoperative PBI and second breast-conserving surgery (BCS) for patients with an ipsilateral recurrent breast event (IRBE) after previous BCT.

**Methods and analysis:**

The REPEAT trial is a multicentre, prospective, single-arm trial investigating ablative single-dose preoperative PBI in patients with an IRBE. Eligible patients are ≥50 years, have a unifocal non-lobular invasive breast cancer ≤2 cm, Bloom-Richardson grade 1 or 2, oestrogen receptor-positive, human epidermal growth factor receptor 2-negative and clinically negative axillary lymph nodes. The study plans to enrol 25 patients. Radiotherapy planning will involve the use of CT and MRI in the treatment position. Single-dose PBI of 20 Gy to the tumour and 15 Gy to the surrounding 2 cm of breast tissue will be delivered using a conventional or MR-guided linear accelerator. Tumour response will be monitored preoperatively using MRI and liquid biopsies to identify biomarkers for evaluating radiosensitivity. BCS will be performed 3 (±one) weeks post PBI. The primary endpoint is the incidence of grade 2 or higher treatment-associated acute toxicity within 90 days. Secondary endpoints include the evaluation of acute (grade 1) and late toxicity, radiologic and pathologic response, mastectomy rate, patient-reported outcomes, cosmetic outcome, local, regional and distant recurrence rates, survival outcome and biomarkers in liquid biopsies and tumour tissue. Patients will be followed up to 5 years after PBI.

**Ethics and dissemination:**

Ethical approval from the Medical Research Ethics Committee of the Amsterdam UMC has been obtained (NL85983.018.24). The results will be disseminated via peer-reviewed academic journal and presentation at conferences. In addition, summaries will be shared with the participating patients.

**Trial registration number:**

The trial was registered prospectively on October 11^th^ 2024 at clinicaltrials.gov (NCT06640881).

STRENGTHS AND LIMITATIONS OF THIS STUDYThis study offers a comprehensive set of outcome measures, providing valuable insights into the safety of preoperative single-dose partial breast irradiation following previous breast-conserving therapy. It also assessed quality of life, cosmetic outcomes and radiosensitivity biomarkers.A notable strength is the study’s design, which allows for easy implementation into clinical practice by conducting axillary surgery as per recommendations of a multidisciplinary tumour board, given the debated value of the sentinel node procedure as a staging tool.We evaluate late toxicity, quality of life, cosmetic outcome and oncological outcomes over a 5-year follow-up.A limitation is the short interval between radiotherapy and surgery, which ensures oncological safety but may not allow sufficient time to observe a radiotherapy-induced pathological tumour response.

## Background

 The majority of patients with early-stage breast cancer are treated with breast-conserving therapy (BCT), consisting of breast-conserving surgery (BCS) followed by whole breast irradiation (WBI) or partial breast irradiation (PBI).^1^,^5^ The 5-year local recurrence rate after BCT is low, 0.5% per year.^6^ However, due to improved breast-cancer survival, the absolute number of patients with an ipsilateral recurrent breast event (IRBE) is increasing.^7^ Current standard for care of an IRBE is salvage mastectomy after previous BCT.^8^

Over the last decades, the interest in second-BCT in patients with a low-risk ipsilateral breast cancer or ductal carcinoma in situ (DCIS) event has increased.^9 10^ These low-risk characteristics are age ≥50 years, invasive tumour size ≤2 cm or DCIS <2.5 cm, Bloom-Richardson grade 1–2, oestrogen (ER)-positive, human epidermal growth factor receptor 2 (HER2)-negative, node negative breast cancer, with a time interval after primary breast cancer ≥2 years.^9 10^ A recent systematic review of single-arm retrospective cohort studies in patients with an IRBE after initial BCT showed weighted estimates for 5-year overall survival (OS) for repeat BCS alone and repeat BCS and postoperative reirradiation of 77.0% (95% CI 76.1% to 78.7%) and 87.3% (95% CI 86.9% to 87.7%), respectively.^9^ 5-year local control was 76.0% (95% CI 74.5% to 76.9%) for repeat BCS and 88.6% (95% CI 87.9% to 89.2%) for repeat BCS followed by postoperative reirradiation.^9^ Two studies on BCS with partial breast reirradiation using external beam radiotherapy (RT) and brachytherapy reported 5-year OS rates of 95% (95% CI 85% to 98%) and 89% (95% CI 86% to 93%), respectively.^6 11^ The 5-year cumulative incidence of IRBE was 5% (95% CI 1% to 13%) and 4% (95% CI 2% to 6%), respectively. Second BCT might not be the preferred treatment for patients who already had poor cosmetic outcome after initial BCT, as reirradiation could worsen cosmetic outcome due to the risk of additional breast fibrosis.

There is increasing interest in preoperative RT in patients with low-risk primary breast cancer, since target definition is more precise and the irradiated volume is smaller compared with postoperative RT.^12 13^ Consequently, preoperative PBI could reduce RT-induced toxicity and improve quality of life (QoL). A smaller volume also enables a higher radiation dose per fraction which results in a reduced number of fractions and overall treatment time. A recent systematic review showed that grade 1 acute skin toxicity (0–34%), grade 1 seroma and grade 1 breast fibrosis (46–100%) were the most frequently reported toxicities.^12^ Cosmetic outcome was good to excellent in 78% to 100% of the patients. After a maximum median follow-up of 5 years, local recurrence rates were 0 to 3% and OS 97–100%.^12^ It is expected that reirradiation using preoperative PBI will lead to smaller irradiated volumes equal to preoperative PBI in primary low-risk breast cancer. This could result in a limited dose to the surrounding organs at risk and could lead to less toxicity and better cosmesis compared with postoperative PBI after second BCS. In addition, the breast tissue exposed to the highest RT dose is excised during surgery, reducing the risk of RT-associated toxicity. To our knowledge, there are no data on preoperative reirradiation in patients with an IRBE after previous BCT.

The REPEAT trial aims to assess the feasibility of single-dose preoperative PBI and second BCS for an IRBE after previous BCT based on grade 2 or higher acute toxicity. Further response assessment modalities will be evaluated to optimise response assessment with radiological evaluation using breast MRI and the analysis of biomarkers in blood and tumour tissue. In addition, acute and late toxicity, pathological response, patient-reported outcome measures (PROMs), cosmetic results and oncological outcomes will be evaluated.

## Methods/design

### Study design

The REPEAT trial is a Dutch multicentre, phase II, single-arm prospective study at the Amsterdam University Medical Center (UMC) and Catharina Hospital Eindhoven in the Netherlands. The trial started in both centres in January 2025 and the estimated end date is December 2032. Eligible patients will be treated with ablative single-dose PBI followed by BCS after 3 (±one) weeks. At baseline (prior to RT) and prior to BCS, toxicity, PROMs and cosmetic outcome will be assessed. Additionally, a preoperative MRI will be performed 3 (±one) weeks following RT to evaluate the acute tumour response. The primary objective is to assess the feasibility of single-dose preoperative PBI and second BCS for an IRBE after previous BCT based on acute toxicity. The secondary objectives are to assess treatment-induced toxicity, radiological and pathological response, mastectomy rate, PROMs, cosmetic results, patient comfort during RT treatment delivery, oncological outcomes and RT-associated immune response markers (CD4, CD8 and FOXP3 expressing T cells) in blood and tumour tissue. All tumour tissue and blood samples of patients will be preserved at the Amsterdam UMC Central Biobank, location Vrije Universiteit Medical Center. This study design is based on the ABLATIVE study in patients with primary low-risk breast cancer, but with a shorter interval between RT and BCS (NCT05350722).^14 15^

### Study population

The study population will consist of women who are 50 years or older with a low-risk IRBE after previous BCT. The definition of low-risk IRBE is based on the ASTRO suitable criteria for PBI.^1^ Patients are eligible for study participation in case of: tumour size ≤2 cm on MRI, unifocal non-lobular invasive carcinoma, Bloom-Richardson grade 1 or 2, ER-positive and HER2-negative, clinical node negative on 18F-fluorodeoxyglucose positron emission tomography computed tomography (FDG PET-CT)/ultrasound/MRI, no distant metastases and no or mild late toxicity (no grade 2 or higher) from previous BCT. The inclusion and exclusion criteria are presented in table 1.

**Table 1 T1:** Inclusion and exclusion criteria

Inclusion criteria	Exclusion criteria
WHO performance status 0–2	Ipsilateral invasive breast cancer event <2 years after first breast-conserving therapy for breast cancer
Women ≥50 years with an ipsilateral invasive recurrent breast cancer event after previous breast-conserving surgery and postoperative whole breast irradiation	Other malignancy within 5 years before ipsilateral breast recurrence diagnosis. For carcinoma in situ, no specific time span to ipsilateral breast recurrence diagnosis is required for inclusion
Tumour size ≤2 cm and unifocal on MRI	Known breast cancer mutation gene carrier
Tumour histology as assessed on biopsy: Bloom-Richardson grade 1 or 2 Non-lobular invasive histological type carcinoma Oestrogen receptor positive HER2 receptor negative No lymphovascular invasion	Collagen synthesis disease (eg,osteogenesis imperfecta, Ehlers-Danlos syndrome, systemic sclerosis)
	Delayed wound healing after primary treatment
No extensive DCIS (outside tumour size of 2 cm) on mammography or tumour biopsy, including non-mass enhancement on MRI	Previous ipsilateral mastectomy
Clinical node negative on 18-F FDG PET-CT, ultrasound and MRI	Invasive lobular carcinoma or DCIS without invasive cancer
No distant metastasis	MRI absolute contraindications and intolerance
No or mild late toxicity (no grade 2 or higher) from previous breast-conserving therapy	Indication for treatment with neoadjuvant chemotherapy
Adequate understanding of the Dutch language	Legal incapacity
	Poor cosmetic outcome after initial breast-conserving therapy

DCIS, ductal carcinoma in situ; FDG PET-CT, fluorodeoxyglucose positron emission tomography computed tomography; HER2, human epidermal growth factor receptor 2.

### Study outcomes

The primary endpoint is the rate of acute ≥grade 2 treatment-induced toxicity within 3 months following preoperative RT, using the Common Terminology Criteria for Adverse Events (CTCAE) V.0 (skin toxicity, breast oedema, breast pain and chest wall pain) and the Clavien-Dindo classification (wound infection). Secondary endpoints are any acute (including grade 1) and late treatment-induced toxicity according to CTCAE V.5.0 and the Clavien-Dindo classification. Radiological response will be assessed using a breast MRI, 3 weeks after RT (preoperatively). Pathological response will be evaluated in the resection specimen. In addition, the mastectomy rate will be assessed 5 years after BCS. PROMs will be evaluated using the European Organization for Research and Treatment of Cancer core-30 and breast cancer-specific questionnaires. Cosmetic outcome will be assessed by the patients using the BREAST-Q questionnaire. The physician will score cosmetic outcome as excellent, good, fair or poor based on changes in breast appearance. Additionally, cosmetic outcome will be evaluated objectively using digital photographs analysed by the BCCT.core software and 3D Vectra XT software. Oncological outcomes will be assessed by evaluating local, regional and distant event rates, and disease-free, breast cancer-specific survival (BCSS) and OS. Disease-free survival is defined from the date of RT to the date of local, regional or distant recurrence. BCSS and OS will be determined from the date of RT to the date of death caused by breast cancer and any cause, respectively. RT-associated (immune-activation/-suppressor) biomarkers in blood and tumour tissue will be explored. An overview of the time points at which the outcomes are assessed is shown in figure 1.

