### Statistical analysis

The sample size calculation is based on the primary endpoint of the rate of grade 2 or higher acute treatment-associated toxicity within 90 days (skin toxicity, breast oedema, breast pain, chest wall pain, wound infection). We expect that 30% of our patients will experience ≥grade 2 acute toxicity following preoperative RT. An unacceptable proportion is considered if acute toxicity is observed in 50% or more of the patients. If, during the study duration, more than 50% of the first 10 patients develop ≥grade 2 acute toxicity, the study will be terminated. Therefore, based on the sample size calculation, which ensures that the CI does not encompass an incidence of 50%, a statistical power of 80% and a two-sided alpha of 0.05, a sample size of 21 patients is determined. Adjusting for a 15% allowance to accommodate patients deemed ineligible, the total required sample size is 25.

The assessment of the proportion of patients experiencing ≥grade 2 acute toxicity will be evaluated, and a 95% CI will be calculated. Grade 1 acute and late treatment-induced toxicity, PROMs and cosmetic results will be compared with baseline using linear mixed models for repeated measures. Radiological and pathological response, mastectomy rate, patient comfort during RT treatment delivery and oncological outcomes will be presented using descriptive statistics. The Kaplan-Meier method will be employed to quantify disease-free, breast cancer-specific and OS. Baseline T-cell levels will be analysed across patients to assess interpatient variability and intrapatient changes between baseline and post-treatment timepoints. Overlap in variance among different response markers will be explored. Additionally, the reproducibility of potential response markers, if applicable, will be investigated.

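### Disease-free survival is defined by recurrence only, so a death without recurrence does not count and the Kaplan-Meier figure can exceed overall survival

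*Protocol article*

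**What the plan says.** The Study outcomes section of the protocol article sets the endpoint: "Disease-free survival is defined from the date of RT to the date of local, regional or distant recurrence". The next sentence brings in death, but only for the other two survival endpoints: "BCSS and OS will be determined from the date of RT to the date of death caused by breast cancer and any cause, respectively". The Statistical analysis section names one estimator for all three: "The Kaplan-Meier method will be employed to quantify disease-free, breast cancer-specific and OS". No section adds death to the DFS definition or names a competing-risk method for it.

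The setting is in the abstract ("The study plans to enrol 25 patients"; "Patients will be followed up to 5 years after PBI") and in the Study population section ("The study population will consist of women who are 50 years or older with a low-risk IRBE after previous BCT"). No upper age limit is stated. The article gives no expected DFS value and bases no sample size on DFS.

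**The concern.** A measure called disease-free survival is read as the probability of being alive and free of disease. Under the stated definition a patient who dies without a recorded recurrence never has an event. Kaplan-Meier has only one other place for her: censored at death, as if she could still recur later.

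Three things follow. The curve lies above the share alive and disease-free as soon as one such death occurs. It can lie above OS, which a true DFS cannot do. It is also not comparable with published DFS figures that count deaths, and the error is in the favourable direction. The Background says that, to the authors' knowledge, there are no data on preoperative reirradiation in this setting, so the 5-year figure may later be used as a reference.

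**Working it through.** **Reproducing a plan figure.** There is none for DFS, so the check is one of logic, followed by an illustration of size.

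**Logic.** Events for DFS are recurrences only (Study outcomes). The estimator is Kaplan-Meier (Statistical analysis). A patient who dies recurrence-free is neither an event nor still under observation, so she leaves the risk set as censored. Hence curve as written ≥ P(alive and disease-free), with strict inequality once there is one recurrence-free death.

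**Inputs, from the Background.** Two studies of repeat breast-conserving surgery with partial breast reirradiation "reported 5-year OS rates of 95% (95% CI 85% to 98%) and 89% (95% CI 86% to 93%), respectively". For the same two studies: "The 5-year cumulative incidence of IRBE was 5% (95% CI 1% to 13%) and 4% (95% CI 2% to 6%), respectively". The pairs are therefore (a) 5% recurrence with 95% OS and (b) 4% recurrence with 89% OS.

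**Assumptions.**
- Cause-specific hazards are constant over 5 years.
- The local recurrence rate stands in for any recurrence, because the article gives no any-recurrence rate for these studies.
- The share of deaths that occur without recurrence is unknown and is varied.

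**Formulas.** Let R be the 5-year cumulative incidence of recurrence as first event and D that of death without recurrence.
- DFS counting deaths = 1 − R − D
- Curve as written = (1 − R − D)^(R/(R + D))

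**Coherence limit.** Deaths after recurrence cannot exceed recurrences, so D ≥ (1 − OS) − R. This is the same as requiring DFS ≤ OS.
- In (a): D ≥ 5% − 5% = 0.
- In (b): D ≥ 11% − 4% = 7%.

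| Case | R | D | Curve as written | DFS counting deaths | Gap |
|---|---|---|---|---|---|
| (a) all deaths recurrence-free | 5% | 5% | 0.900^(5/10) = 94.9% | 90.0% | 4.9 points |
| (a) half the deaths recurrence-free | 5% | 2.5% | 0.925^(5/7.5) = 94.9% | 92.5% | 2.4 points |
| (b) all deaths recurrence-free | 4% | 11% | 0.850^(4/15) = 95.8% | 85.0% | 10.8 points |
| (b) smallest coherent D | 4% | 7% | 0.890^(4/11) = 95.9% | 89.0% | 6.9 points |

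In both rows of (b) the curve as written lies above the 89% OS.

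**Sensitivity to how the rates are read.** If in (a) the 5% recurrence and the deaths are treated as independent net risks, the curve is 95.0%. Counting deaths then gives 0.95 × 0.95 = 90.25% (all) or 0.95 × √0.95 = 92.6% (half). The gaps are 4.75 and 2.4 points, so the picture does not change.

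**In patients.** 25 × 5% = 1.25 and 25 × 11% = 2.75 deaths are expected, against 25 × 4% = 1.0 to 25 × 5% = 1.25 recurrences. With complete follow-up each recurrence-free death lowers a true DFS by 1/25 = 4 points and leaves no drop in the curve as written.

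**The case against.** The strongest points on the other side are these.

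- **Censoring is inferred.** The article never says that deaths are censored, and a condensed article may leave censoring rules to a fuller document. This limits the wording but not the point: the event definition is stated explicitly, and with Kaplan-Meier it leaves no other treatment of a recurrence-free death.
- **The recurrence input is local only.** The defined endpoint also counts regional and distant recurrence. A patient who dies of breast cancer after a recorded distant recurrence is already a DFS event. With a higher any-recurrence rate, more of the deaths could follow a recurrence and the gaps would shrink. This stands, so the figures are an illustration.
- **The gap may be zero.** If nobody dies recurrence-free, the two curves are identical. In case (a) that is arithmetically possible. This also stands.
- **Little depends on DFS.** It is one of many secondary outcomes in a single-arm feasibility trial, with no DFS threshold or test, and OS is reported beside it. This stands and limits the weight of the point.

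A reader might go further in four ways that the documents do not support.

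1. *Recurrence risk is materially inflated.* One minus the Kaplan-Meier curve does exceed the cumulative incidence, but here only by 5.1% against 5.0% in (a) and 4.2% against 4.0% in (b), or 0.1 to 0.2 points. Recurrence rates are also to be reported separately and descriptively.
2. *Kaplan-Meier for breast cancer-specific survival is the same error.* That endpoint is defined by breast cancer death. Censoring other deaths is a common cause-specific estimate, and in 25 patients a different method is largely a preference.
3. *Half of the deaths in (b) could be recurrence-free, for a smaller gap.* That would give 1 − 0.04 − 0.055 = 90.5%, above the 89% OS. It needs 5.5% of patients to die after recurrence when only 4% recur, so on these inputs it is impossible.
4. *The feasibility conclusion is at risk.* It rests on acute toxicity and does not use DFS.

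**Conclusion.** The point holds as a defect of definition. The endpoint as written is a recurrence-free interval carrying the name of disease-free survival. It overstates the share alive and disease-free if any patient dies without recurrence, and it may be reported above OS.

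On the article's own background rates the overstatement at 5 years is about 2.4 to 5 points in the first case (half to all deaths recurrence-free) and about 7 to 11 points in the second. Both rest on constant hazards, on local recurrence standing in for any recurrence, and on an assumed share of recurrence-free deaths. They show what could happen and are not a forecast for this trial. The 4 points per recurrence-free death in 25 patients does not depend on those background rates, only on complete follow-up.

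The change is worth making, but the primary endpoint, the sample size and the early termination rule are unaffected.

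**What to change.** Either of two changes resolves it.

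- **Preferred:** define DFS as time from radiotherapy to the first of local, regional or distant recurrence or death from any cause, and keep Kaplan-Meier.
- **Alternative:** keep the recurrence-only endpoint, rename it *recurrence-free interval*, and report it as cumulative incidence with death as a competing event.

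The cost is one definition sentence and, for the alternative, one analysis line. No new data are needed, because deaths are already collected for OS. The downside of the preferred change is that the DFS figure becomes slightly less favourable. The estimated end of the trial is December 2032, so the definition can be corrected well before the 5-year results are analysed.

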**Figure 1 F1:**
[figure not shown]
Overview of outcome assessments. Time point in orange after RT. Time points in green after breast-conserving surgery (BCS). Patient questionnaires include evaluation of cosmetic outcomes and QoL. QoL, quality of life; RT, radiotherapy; w, weeks; y, years.

### Procedures

A flow diagram of the study procedures in the REPEAT trial is shown in figure 2. The surgeon, oncologist or nurse practitioner at the outpatient surgery centre will inform patients about the study during their consultation. If an eligible patient expresses interest, the professional will provide written study information and informed consent forms. Subsequently, the patient will have a consultation with a radiation oncologist at the department of radiation oncology for evaluating the inclusion and exclusion criteria. The patient signs the informed consent forms at the department of radiation oncology after a minimum of 2 days to consider study participation.

